***Sampling method***

After the study proposal is approved by the Ethics Committee of Tehran University of Medical Sciences, and after obtaining a Clinical Trial Registration Code (IRCT) and a written letter of introduction, eligible women will be enrolled in the study. Ethical conditions and considerations will be explained, and written informed consent will be obtained from those willing to participate. The researcher will first provide detailed information about the study, including its title, objectives, inclusion criteria, and the study's procedures. Participants will then be randomly assigned to either the intervention or control group using block randomization. Specifically, volunteers who agree to participate will be randomly allocated to the intervention or control groups using a block size of four. The educational intervention will be conducted in person. The intervention group will receive training based on the Health Belief Model, focusing on its constructs, in four sessions of 45-60 minutes each, held once a week with groups of 10-15 participants. This training will be provided by the researcher. The control group will receive routine care. The questionnaires will be administered to participants in both groups at three time points: before the intervention, immediately after, and 8 weeks post-intervention. To adhere to ethical considerations, the control group, if interested in receiving the training, will be provided with educational pamphlets and CDs after the intervention is completed. Figure 2 shows the schedule of enrolment, intervention, and assessment.

Figure 2. Schedule of enrolment, interventions, and assessments

|  | **STUDY PERIOD** | | | | | | | |  |
| --- | --- | --- | --- | --- | --- | --- | --- | --- | --- |
|  | **Enrolment** | **Allocation** | **Post-allocation** | | | | **Close-out** | |  |
| **TIMEPOINT**** | ***-t_1_*** | **0** | ***t_1_*** | ***t_2_*** | ***t_3_*** | ***t_4_*** | | ***t_5_*** | |
| **ENROLMENT:** |  |  |  |  |  |  | |  | |
| **Eligibility screen** | X |  |  |  |  |  | |  | |
| **Informed consent** | X |  |  |  |  |  | |  | |
| ***Randomized by independent person*** | X |  |  |  |  |  | |  | |
| **Allocation** |  | X |  |  |  |  | |  | |
| **INTERVENTIONS:** |  |  |  |  |  |  | |  | |
| ***Group A: educational intervention*** |  |  |  |  |  |  | |  | |
| ***Group B: control*** |  |  |  |  |  |  | |  | |
| **ASSESSMENTS:** |  |  |  |  |  |  | |  | |

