***Sample Size***

To determine the necessary sample size, with a confidence level of 95%, a test power of 80%, and assuming that the effect size (Cohen's d) of the intervention compared to the control group is 0.7 [22,23], the minimum sample size required for each group is calculated to be 32 participants. Considering a 10% dropout rate, the sample size for each group will be set at 35 participants.

n = (2 × (z _(1-α/2)_ + z _(1-β)_))^2^ / (E × S)^2^ = (2 × (1.96 + 0.84))^2^ / (0.7)^2^ = 32

z _(0.975)_ = 1.96

z _(0.8)_ = 0.84

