***Outcomes***

The primary outcome of the study is sexual self-care which will be measured through the sexual self-care in women of reproductive age (FSHS) questionnaire. The secondary outcome of the study will be participants’ perceived Susceptibility, severity, benefits, barriers, and self-efficacy regarding sexual self-care which will be measured through the researcher-designed questionnaire based on the HBM.

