***Data management and analysis***

Descriptive analysis will be used to report baseline characteristics. For continuous variables with a normal distribution, ANOVA will be used between subjects, and for continuous variables without a normal distribution, the Friedman test will be employed. The effectiveness of the intervention will be evaluated using ANOVA, and the impact of demographic variables on sexual self-care will be determined using logistic regression modeling. All statistical analyses will be performed using SPSS version 24. All statistical analyses will be performed using the per protocol analysis and at a significance level of less than 0.05.

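### The test that decides effectiveness is not pinned down: a between-subject ANOVA with no baseline term, and two FSHS follow-ups with neither named primary

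*Protocol*

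**What the plan says.** In the protocol, the section on data management and analysis says that "The effectiveness of the intervention will be evaluated using ANOVA". For continuous variables it gives a between-subject ANOVA if they are normally distributed and the Friedman test if they are not. All tests are run "at a significance level of less than 0.05". The section mentions no covariate, no repeated-measures or arm-by-time term, and no rule for combining time points.

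The Outcomes section states: "The primary outcome of the study is sexual self-care which will be measured through" the FSHS questionnaire. No time is attached. The Sampling method section has the questionnaires given to both groups at "three time points: before the intervention, immediately after, and 8 weeks post-intervention". The Intervention Design section repeats these times, and secondary objective 1 lists the same three. None of these places ranks one follow-up above the other.

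The Sample Size section plans a single two-group comparison "with a confidence level of 95%, a test power of 80" percent, "assuming that the effect size (Cohen's d) of the intervention compared to the control group is 0.7". From this, "the minimum sample size required for each group is calculated to be 32 participants", raised to 35 for dropout.

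**The concern.** Two decisions that fix the primary claim are left open.

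- **Baseline.** Baseline FSHS probably predicts later FSHS. A between-subject comparison without it carries that predictable variation as noise, and leaves any chance baseline difference between the arms in the estimate. The trial is sized with almost no power to spare, so this matters.
- **Time point.** With two follow-ups and no ranking, the reader cannot tell before the data are seen which arm difference decides whether the education worked. A single planned comparison could become two chances of success.

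The fallback adds to the uncertainty. The Friedman test compares related measurements within the same women, so it cannot test a difference between two independent arms.

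**Working it through.** **Inputs from the protocol.** Two-sided alpha 0.05 (z = 1.96), power 80% (z = 0.84), d = 0.7, 32 per group before dropout, 10% dropout, 35 per group randomised.

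**Assumptions.** The correlation r between baseline and follow-up FSHS is not given. I use 0.3, 0.5 and 0.7. The stability coefficient of 0.97 in the instrument section describes the questionnaire's reliability, not the correlation over this trial's follow-up, so I do not use it.

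**1. Reproduce the plan's figure.** n = 2 × (1.96 + 0.84)² / 0.7² = 2 × 7.84 / 0.49 = 32 per group. This matches the stated 32. (The printed formula has a misplaced bracket and would give 64; that is a separate matter.) The calculation is for an unadjusted two-group comparison at one time. After dropout, 35 × 0.9 = 31.5, taken as 31 per arm.

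**2. Power without baseline.** The noncentrality is 0.7 × √(31/2) = 2.76 on 60 degrees of freedom, which gives power of 77.4%. At 32 per arm it is 78.7% by the t distribution and 80.0% by the normal approximation.

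**3. Power with baseline adjustment (ANCOVA, one named time, 31 per arm).** The residual SD shrinks by √(1 − r²), so the effective d is 0.7 / √(1 − r²). The last column is explained in step 4.

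| r (assumed) | Effective d | ANCOVA power | Group-by-time power |
| --- | --- | --- | --- |
| 0.3 | 0.734 | 81% | 66% |
| 0.5 | 0.808 | 88% | 81% |
| 0.7 | 0.980 | 97% | 96% |

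**4. If a repeated-measures ANOVA was meant.** Take an arm difference of 0 at baseline and 0.7 at both follow-ups, with equal correlation r between all times. The group-by-time F test has 2 and 120 degrees of freedom and noncentrality (31/2) × 0.7² × (2/3) / (1 − r) = 5.06 / (1 − r), that is 7.2, 10.1 and 16.9. Its power, in the last column, is at or below that of ANCOVA at each of these correlations. The other test in that model, the between-subject main effect averaged over all three times, dilutes the effect with baseline. At 32 per arm its power is about 72%, 63% and 55%.

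**5. Two follow-ups, success on either.** With each tested at 0.05, type I error is 1 − 0.95² = 9.75% if the two tests are independent. At correlations of 0.3, 0.5, 0.7 and 0.9 between the tests it is 9.5%, 9.1%, 8.3% and 7.0%. This applies only if success on either one is claimed.

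**6. Chance imbalance.** With 32 per arm the baseline difference between arms has an SD of √(2/32) = 0.25 SD units, and a 95% range of about ±0.49.

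**The case against.** **A repeated-measures ANOVA may have been intended.** Friedman is a repeated-measures test, and the objectives compare scores over three times. In a two-group repeated-measures model, baseline is one level of time and is not ignored. This stands as far as it goes: the text does not settle which ANOVA is meant, and the loss in step 3 applies to the literal reading only. It does not rescue the plan, because that model still names no deciding test and, at the correlations shown, gains nothing over ANCOVA.

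**Covariates may sit in a statistical analysis plan that is not at hand.** That is possible, and silence on covariates alone would be no finding. But the protocol does state a between-subject ANOVA, and the time of the primary outcome is a protocol-level item.

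**The unadjusted test is valid.** This is correct. Randomisation makes it unbiased on average, and its standard error already allows for chance imbalance. Adjustment is a gain in efficiency, not the repair of an invalid test.

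A reader might also infer more than the documents support:

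- **That the type I error is 7% to 9.5%.** No passage states an either-time success rule, and a single group-by-time test would be one test at 0.05.
- **That the immediate post-intervention assessment was left out of the schedule.** Figure 2, as extracted, marks the FSHS and HBM questionnaires only at enrolment and in the final column. But the table is broken and its intervention rows are empty, so the original figure must be checked first.
- **That teaching in groups of 10 to 15 invalidates the ANOVA.** The protocol gives no intra-class correlation, so any figure would rest on an assumed one, with only about three groups in one arm.

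**Conclusion.** The point holds in this form: the protocol fixes neither the model nor the time point that decides effectiveness, and its literal wording leaves out a baseline measurement that every woman provides. On that reading the cost is about 4, 11 and 19 percentage points of power (77% against 81%, 88% and 97%) at assumed correlations of 0.3, 0.5 and 0.7, with d = 0.7 and 31 analysed per arm. Even the lowest of these correlations brings power back above the planned 80%. The comparison is not biased on average by omitting baseline. The inflation to about 7% to 9.5% is conditional on success being claimed at either follow-up. This should be changed before analysis, but it does not make the trial invalid.

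**What to change.** - State the primary analysis as ANCOVA of FSHS adjusted for baseline FSHS, or a linear mixed model with the same adjustment.
- Name one follow-up in advance as the primary contrast, reported as the arm difference with its 95% confidence interval, and make the other secondary. Eight weeks is one option. The documents favour neither time, so the choice is the sponsor's.
- Remove the Friedman test as a test of the arm difference.
- Check the original Figure 2 against the three assessments in the Sampling method and Intervention Design sections, and reconcile them if the immediate post-intervention mark is missing.
- Optionally, record each woman's teaching group for a sensitivity analysis. About three groups estimate the group variance poorly, so little weight should rest on it.

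The cost is protocol wording and a slightly fuller analysis. No extra participants or questionnaires are needed.

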According to the results of a qualitative study conducted in Iran (2023), most women infected with HPV lacked sufficient knowledge about the virus, including its causes, symptoms, complications, prevention, and screening methods. Education, counseling, support, and healthcare services were identified as the main needs and challenges in reproductive and sexual health [17]. Based on the literature review, most studies have focused on the prevention of HPV infection. However, individuals who are already affected by this condition face numerous challenges, highlighting the need for further research into self-care practices for this group of patients. Given the Iranian and Islamic cultural context, HPV infection may be associated with negative psychological effects and significant challenges for Iranian women due to its sexual nature and the stigma attached to it, complicating efforts to educate, support, and address their needs [18,19]. Therefore, the present study aims to examine the impact of an educational intervention based on the Health Belief Model on sexual self-care among women of reproductive age infected with HPV.

**Hypothesis:** The educational intervention based on the Health Belief Model will lead to changes in perceived susceptibility, severity, benefits, barriers, and self-efficacy among women with HPV. These changes will, in turn, modify individual behavior and enhance sexual self-care in those affected by this disease.

**Objectives:** The primary objective of this study is to evaluate the effectiveness of an educational intervention based on the Health Belief Model on sexual self-care among women infected with the HPV. The secondary objectives of the study are:

1. To determine and compare the sexual self-care scores among women with HPV in the intervention and control groups before, immediately after, and 8 weeks following the intervention.
2. To determine and compare the items of the Health Belief Model (perceived susceptibility, perceived severity, perceived benefits, perceived barriers, cues to action, and self-efficacy) regarding sexual self-care among women with HPV in the intervention and control groups before, immediately after, and 8 weeks following the intervention.

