***Study instruments***

The three study instruments are explained in what follows.

**-****Demographic and obstetric information questionnaire**: It consists of 16 questions including: Age, Spouse's Age, Education Level, Spouse's Education Level, Employment Status, Spouse's Occupation, Income Level, Duration of Marriage, Number of Pregnancies, Number of Deliveries, Type of Delivery, Number of Abortions, Contraceptive Method, History of Pap Smear, History of HPV Vaccination, Duration of HPV Infection Based on Diagnostic Tests.

-**The Sexual Self-Care in Women of Reproductive Age (****FSHS) questionnaire**: It consists of 40 items scored on a 5-point Likert scale ranging from Never (1) to Always (5) across 4 domains: prevention of sexually transmitted infections (STIs), prevention of gynecological cancers, prevention of unintended pregnancies, and promotion of sexual health. Developed using a deductive approach based on the Waltz model in 2021 by Yazdani and colleagues in Iran, the tool has demonstrated a content validity index (CVI) of 0.93, a content validity ratio (CVR) of 0.96, and a high internal consistency reliability with a Cronbach's alpha of 0.94. The stability of the instrument, measured by intra-cluster correlation, was 0.97 (confidence interval: 0.94-0.98), indicating strong validity and reliability in the Iranian population, making it a suitable measure of sexual self-care [24].

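### Logistic regression is named for the demographic analysis of sexual self-care, but the protocol defines and analyses that outcome as a numeric score and gives no cut-off, category or ordinal form

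*Protocol*

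**What the plan says.** The Outcomes section states: "The primary outcome of the study is sexual self-care which will be measured through the sexual self-care in women of reproductive age (FSHS) questionnaire". Study instruments describes the scale: "It consists of 40 items scored on a 5-point Likert scale ranging from Never (1) to Always (5) across 4 domains". The same section describes the demographic and obstetric questionnaire, the source of the candidate predictors: "It consists of 16 questions including" a list running from age and education to contraceptive method, vaccination history and time since HPV diagnosis.

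Two analyses of this outcome share one sentence in Data management and analysis. For the treatment effect: "The effectiveness of the intervention will be evaluated using ANOVA". For the covariates: "the impact of demographic variables on sexual self-care will be determined using logistic regression modeling". The Abstract repeats logistic regression in its list of methods.

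The protocol gives no threshold for adequate self-care, no responder definition and no ordered categories. It does not say that the logistic model is ordinal, or how many of the 16 items would enter it.

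**The concern.** Logistic regression in its usual sense models a two-level outcome. The FSHS is not two-level as the protocol describes it, and the protocol's other statements all treat it as numeric. The first secondary objective is "To determine and compare the sexual self-care scores among women with HPV in the intervention and control groups". The Sample Size section rests on a standardised mean difference, the Discussion would read a rise in scores as a sign of benefit, and ANOVA is applied to the outcome in the very sentence that names the logistic model.

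Anyone following the text with a binary model must first cut the score somewhere. The cut discards information, and the associations reported can depend on where it falls. What is at stake is the reliability of statements about which demographic characteristics go with better or worse self-care, each to be judged at the 0.05 level in at most 70 women.

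**Working it through.** **Inputs.** 40 items scored 1 to 5, and 16 demographic and obstetric items (Study instruments). 32 per group before dropout, 35 per group after a 10% allowance, d = 0.7 (Sample Size). Per-protocol analysis at 0.05 (Data management and analysis). At most 70 women are analysed, or about 64 (2 × 32) after dropout.

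**1. The plan's own figure.** The protocol gives no figure for the logistic model. Its one sample-size result is 32 per group, which follows from 2 × (1.96 + 0.84)² / 0.7² = 15.68 / 0.49 = 32.0, with the leading 2 outside the square. This is a formula for comparing two means, so the trial was sized on a numeric outcome.

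**2. The outcome scale.** If the items are summed, the range is 40 × 1 = 40 to 40 × 5 = 200, which is 161 possible values. Summing is inferred, because the protocol speaks of scores without giving a scoring rule.

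**3. Information kept after a split.** For a normally distributed score cut at quantile q, the asymptotic share of information kept is φ(z_q)² / [q(1 − q)], where φ is the standard normal density.

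| Split | Share kept |
| --- | --- |
| 50/50 | 2/π = 63.7% |
| 30/70 | 57.6% |
| 20/80 | 49.0% |

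At the median, 70 women count as 70 × 0.637 ≈ 45. A less even split loses more.

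**4. Power for one demographic predictor.** Simulation with 2,000 runs per setting, N = 70, one normal predictor with correlation r to the score, two-sided 0.05:

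| r | Linear regression on the score | Logistic regression on a median split |
| --- | --- | --- |
| 0.3 | 71% | 47% |
| 0.4 | 94% | 77% |

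The values of r are illustrative, since the protocol states none.

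**5. Events per variable if all 16 items enter (assumption).** With a median split and one parameter per item, 35/16 = 2.2 at N = 70 and 32/16 = 2.0 at N = 64. If dummy coding of multi-category items raised the count to 25 parameters (also an assumption), 35/25 = 1.4. A 30/70 split with 16 parameters gives 21/16 = 1.3.

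**6. What that does, and whether a linear model escapes it.** Simulation with 16 pure-noise normal predictors, 2,000 runs per setting:

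| N | Logistic: mean apparent AUC | Logistic: Wald type I error | Linear: type I error | Linear: mean R² |
| --- | --- | --- | --- | --- |
| 70 | 0.78 | 7.5% | 4.4% | 0.23 |
| 64 | 0.79 | 8.6% | 5.4% | 0.25 |

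The linear tests stay near 5%, but R² is still about 0.23 from noise alone, as expected from 16/69 = 0.23. That model has only 70/16 = 4.4 women per predictor. Changing the model removes the information loss. Only a shorter predictor list removes the overfitting.

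**The case against.** Much can fairly be said on the other side.

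- **The text does not say binary.** A reader might infer that the stated analysis cannot be run at all. The documents do not support that: an ordinal logistic model can take an ordered score without a split. But the protocol does not name one, so the mismatch stands as an ill-chosen or under-specified model.
- **A cut-off could be set elsewhere.** A reader might infer that a threshold would be picked after seeing the data. The statistical analysis plan is not at hand and could fix one in advance. A missing cut-off alone would be a detail left to that plan. What is open to criticism is the model that the protocol does state for an outcome it treats as a score.
- **Sixteen predictors is not in the text.** The protocol does not say that every item enters one model. About 2 events per variable is the all-items case, and a linear model with all 16 would be stretched too. In the simulation with all 16 items, failure to fit was almost absent (at most 0.05% of runs), although sparse categorical predictors were not simulated.
- **The treatment comparison is not touched.** A reader might infer that the trial's main test loses power. It does not, because effectiveness is assigned to ANOVA.
- **No analysis of who benefits is planned.** A reader might take the logistic model as a search for women who respond to the education. The sentence concerns association with self-care, and no subgroup or arm-by-covariate analysis is described.
- **The analysis is minor.** It is neither the primary objective nor one of the two listed secondary objectives.

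These points limit the size of the finding. None reconciles logistic regression with a 40-item score that has no stated cut-off, category or ordinal form.

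**Conclusion.** The point holds as a limited finding about a secondary analysis. The named model does not fit the outcome as the protocol defines and otherwise analyses it. Read as ordinary binary logistic regression, it would discard about 36% of the information (100% − 63.7%) at the best possible split. In the illustrative case of r = 0.3 and N = 70, power falls from about 71% to about 47%.

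These sizes assume a summed, roughly normal score and a median split, and the power figures also assume a single normal predictor. The figure of about 2 events per variable further assumes that all 16 items are entered. The planned comparison of the arms is unaffected, so the correction is worth making but is not critical to the trial's main conclusion.

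**What to change.** In Data management and analysis, and in the Abstract's list of methods, replace logistic regression with multiple linear regression of the FSHS score, at a follow-up time point named in advance, on baseline FSHS, arm and a short prespecified list of demographic variables. Label it exploratory. State how the FSHS total is formed. The list should be well short of 16 items, because the change of model alone does not cure overfitting.

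If the authors do want a categorical or ordinal analysis, the protocol should name the ordinal model, or define the category and its basis before any outcome data are examined.

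The cost is wording in two places. Baseline and follow-up FSHS and the demographic items are already to be collected, and the planned software fits the linear model.

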***Exclusion Criteria***

- - Absence from more than two educational sessions
  - Incomplete or incorrect completion of the questionnaire
  - Lack of willingness to continue participating in the study

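### The only planned analysis is per protocol, and one of its three removal rules, session attendance, can take out intervention women only, so randomisation no longer protects the comparison

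*Protocol*

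**What the plan says.** The analysis set is fixed in one sentence under Data management and analysis: "All statistical analyses will be performed using the per protocol analysis and at a significance level of less than 0.05". Neither an intention-to-treat nor an all-randomised set appears anywhere in the protocol.

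The per-protocol set is not defined separately. The only stated grounds for removing a woman are the three items under Exclusion Criteria:

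- "Absence from more than two educational sessions"
- "Incomplete or incorrect completion of the questionnaire"
- "Lack of willingness to continue participating in the study"

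The participant flow chart (Figure 1) also has a box for women excluded from analysis.

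Two statements under Sampling method settle which arm each rule can reach. On treatment: "The control group will receive routine care". On measurement: "The questionnaires will be administered to participants in both groups at three time points: before the intervention, immediately after, and 8 weeks post-intervention".

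The aim is given at the end of the Background: "The primary objective of this study is to evaluate the effectiveness of an educational intervention based on the Health Belief Model on sexual self-care".

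**The concern.** A per-protocol set chosen partly by behaviour after allocation is no longer a randomised comparison. The attendance rule makes this one-sided. An intervention woman who comes to none or one of the four sessions leaves the analysis. The control women who would have behaved the same way cannot be identified, so they stay. The contrast becomes sufficient attenders against all controls, which is not the effect of offering the programme.

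The protocol gives reason to think attendance and outcome may be linked. Its description of perceived benefits, a secondary outcome, ties that belief to steady participation in sessions. Its Discussion says stigma and psychological difficulty can stand in the way of receiving education. The Discussion also plans to recommend the programme to health professionals if it works, and that decision needs the effect in all women to whom it is offered.

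This is a positive statement covering every analysis, the primary one included. It is not a detail left open for a statistical analysis plan.

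**Working it through.** **1. Which rule reaches which arm**

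| Rule | Timing | Arm |
|---|---|---|
| Absent from more than 2 of 4 sessions | Necessarily after allocation | Intervention only |
| Incomplete or incorrect questionnaire | Not stated; a baseline form could be faulted before allocation, follow-up forms only after | Either |
| Unwilling to continue | Not stated; mainly after enrolment | Either |

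One rule of three is specific to an arm.

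**2. The plan's own figures.** The Sample Size section gives d = 0.7, 95% confidence, 80% power, 10% dropout, 32 per group, set at 35. The standard formula reproduces the 32:

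2 × (1.96 + 0.84)² / 0.7² = 2 × 7.84 / 0.49 = 32.0

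(33 with unrounded z values). For dropout, 32 / 0.9 = 35.6 and 32 × 1.1 = 35.2, so 35 is within rounding. None of these figures says how many women will miss sessions or how they differ.

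**3. Bias from the attendance rule.** Assume a share p of women in each arm are of the non-attending kind and would score D SD below the rest whatever their allocation. Let attenders have mean m and let there be no treatment effect.

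- Intervention mean after removal: m
- Control mean, nobody removed: (1 − p)m + p(m − D) = m − pD
- Bias: p × D

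p and D are assumptions. Only p = 10% has any anchor, the dropout allowance, and that is not tied to attendance.

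**4. Type I error.** Simulation with no true effect, 35 per arm, absentees removed from the intervention arm only, 15,000 runs. The normal approximation uses SE = √(1/(35(1 − p)) + 1/35), which is 0.246 at p = 10% and 0.254 at p = 20%. It adds the two tail areas beyond ±1.96 after a shift of pD/SE.

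| p | D | Bias (SD) | pD/SE | Approximation | Simulated |
|---|---|---|---|---|---|
| 10% | 0.5 | 0.05 | 0.20 | 5.5% | 5.4% |
| 10% | 1.0 | 0.10 | 0.41 | 6.9% | 6.3% |
| 20% | 0.5 | 0.10 | 0.39 | 6.8% | 6.9% |
| 20% | 1.0 | 0.20 | 0.79 | 12.4% | 11.1% |

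The approximation runs higher at D = 1.0, in part because it ignores the spread that the would-be non-attenders add to the control arm.

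**5. A second model.** Attendance propensity is correlated rho with outcome, and the k lowest of 35 intervention women are removed (40,000 runs, no true effect).

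| k removed | Bias, rho = 0.3 | Type I error | Bias, rho = 0.5 | Type I error |
|---|---|---|---|---|
| 2 | 0.03 | 5.1% | 0.06 | 6.0% |
| 4 | 0.06 | 5.8% | 0.10 | 7.6% |
| 7 | 0.10 | 7.1% | 0.17 | 11.0% |

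At rho = 0 the bias is zero and the error about 5%. Analysing all randomised women also gives about 5% throughout.

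**6. What an all-randomised analysis would show.** Suppose d = 0.7 holds in attenders and non-attenders gain nothing.

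- 4 of 35 do not attend: 0.7 × 31/35 = 0.62; simulated power about 69–72%.
- 7 of 35 do not attend: 0.7 × 28/35 = 0.56; simulated power about 59–62%.

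**The case against.** A reader might infer that the removal rules mostly strike the intervention arm. They do not. Both arms complete the questionnaires and either arm can withdraw. Only attendance is one-sided.

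A reader might also infer that the result is certain to be biased towards benefit. That requires poor attenders to be women who would have scored lower anyway. The protocol makes this plausible but gives no figure for it. Women already confident in their self-care might skip sessions instead, which would push the bias the other way. With no link between attendance and outcome, the null bias is zero.

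The attendance rule is lenient as well. A woman must miss three or four of four sessions, so p = 20% means one in five receives at most one session. At 10% the error inflation is modest, and nothing in the protocol supports a D as large as 1.0.

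Finally, the protocol does not say what counts as incomplete. One cannot assume that a single blank item among the 40 self-care items would remove a woman.

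All of this stands, and it limits the claim about size and direction. It does not touch the central point: the sole analysis set is chosen partly by behaviour after allocation, and one of the criteria exists in one arm only.

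**Conclusion.** The point holds. The planned analysis gives up the protection of randomisation for an objective framed as effectiveness, and no all-randomised result is planned to set beside it.

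The loss of protection is certain. The direction and size of the bias are conditional. At the protocol's 10% attrition figure, with D assumed between 0.5 and 1.0, the distortion is 0.05 to 0.10 SD and type I error about 5.4% to 6.3%. At an assumed p of 20% it is 0.10 to 0.20 SD, at most 29% of the planned 0.7 (0.20/0.7), and about 7% to 11%. These figures illustrate the attendance rule alone. Removals under the other two rules could add to the bias or offset it, and the protocol gives no basis for a number.

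It should be corrected before the analysis, and preferably while follow-up can still be collected, because outcomes not sought from non-attenders are hard to recover later.

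**What to change.** - Make the primary analysis include every randomised woman in her allocated arm, whatever her attendance.
- Stop using attendance as a reason for removal from analysis.
- Seek both follow-up questionnaires from non-attenders who still consent.
- Treat withdrawal and incomplete forms as missing data and not as grounds for exclusion. Deleting the withdrawal rule would not recover answers that a woman does not give; the method for missing data can be set in the statistical analysis plan.
- Keep per protocol as a labelled sensitivity analysis with a stated definition.

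The cost is a wording change, follow-up forms from a few women, and a somewhat smaller estimated effect. Power also has to be faced. If 0.7 applies only to attenders and 4 of 35 do not attend, the all-randomised effect is about 0.62 and power about 69–72%. The Sample Size section should therefore say that its 80% is conditional on d = 0.7 across all randomised women, or re-justify 35 per arm for a diluted effect.
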